## Abstract

Rising temperatures in Africa present an increasing threat to agricultural productivity and public health, particularly among subsistence farming communities reliant on rain-fed agriculture. Heat exposure can impair farmers’ work capacity, disrupt harvests, and heighten health risks, especially for young children vulnerable to undernutrition. The Heat to Harvest (H2H) study investigates how environmental heat exposure influences farmers’ physiological and behavioral responses, and how these in turn affect harvest yields and child nutrition. It also examines differences in labor performance and recovery between households with and without cool roof coatings, although this intervention is not the central focus. H2H is designed as a prospective cohort study nested within two Health and Demographic Surveillance Systems (HDSS) in Nouna, Burkina Faso, and Siaya, Kenya. The study integrates environmental monitoring (temperature and humidity sensors used to compute Wet Bulb Globe Temperature), biometric data (via wearables tracking heart rate, temperature, physical activity, energy expenditure, and sleep), and GPS tracking (capturing spatial mobility and labor duration). The study is embedded within a larger cluster-randomized controlled trial, facilitating comparative analysis under varying thermal conditions. Findings will provide evidence-based insights into how climate-related heat stress affects health and agricultural outcomes, supporting the development of targeted adaptation strategies to enhance resilience, health, and food security in vulnerable farming communities.

## Background

Burkina Faso and Kenya are highly vulnerable to climate change due to their reliance on rain-fed agriculture, which supports a significant portion of their populations and serves as a fundamental pillar of their economies [1–4]. Both countries exhibit low adaptive capacity, driven by limited economic resources for implementing adaptation strategies, a high prevalence of climate-sensitive diseases, and rapid population growth, which exacerbates competition for already scarce resources such as arable land and water [5–10]. The agricultural sector, a cornerstone of economic stability in both countries, faces considerable challenges due to its lack of diversification, making it highly susceptible to climate variability [11,12]. Subsistence farming is the predominant agricultural model, with approximately 86% of households relying on their own agricultural yields for food security [13,14]. This dependence renders farming communities particularly vulnerable to erratic weather patterns and limits their financial capacity to buffer against poor harvests. Climate change further exacerbates agricultural output declines, food insecurity, and nutritional deficiencies [15]. In Burkina Faso, land degradation is a pressing issue, with approximately 33% of land classified as degraded. The country loses an estimated 360,000 hectares to desertification annually, equivalent to 1.3% of its total land area [16]. Additionally, climate change is accelerating soil nutrient depletion and altering plant physiology in both Burkina Faso and Kenya, leading to reduced crop nutrient content and worsening malnutrition [17]. Climate change also drives an increase in pest populations and the spread of plant diseases, further compromising crop yields, while heightened evaporation rates reduce water availability for agriculture [18–20]. Projections for West Africa indicate that climate change could lead to substantial declines in crop yields by 2050, with anthropogenic influences already contributing to shifts in microclimatic conditions [21–25]. Both Burkina Faso and Kenya have experienced rising temperatures, with Burkina Faso recording an average temperature increase of approximately 1°C since the early 2000s [26]. This warming trend has been accompanied by more frequent and intense heatwaves and extreme rainfall events, contributing to significant reductions in regional crop yields. Simulation models predict millet yield losses of 10–20% and sorghum losses of 5–15% under current climate change trajectories [26].

The health impacts of climate change are primarily driven by rising temperatures and increased heat exposure, which are projected to contribute to a surge in heat-related morbidity and mortality, including conditions such as heat stress, cardiovascular diseases, and renal dysfunction [9]. Additionally, climate change is expected to exacerbate the burden of communicable diseases such as dengue fever, pathogenic *Vibrio* infections, and malaria, as warmer and more humid conditions enhance the suitability for vector proliferation and disease transmission [9]. Changes in rainfall and temperature patterns are likely to affect mosquito breeding cycles, further increasing malaria risk [9]. Notably, malaria, pneumonia, and diarrheal diseases together account for nearly half of all deaths in children under five in sub-Saharan Africa (SSA) [27]. In the Kossi region of northwestern Burkina Faso, shifting seasonal weather patterns, rising temperatures, and extreme weather events, including heavy rainfall and flooding, have been associated with direct health impacts, including increased incidences of heatstroke and malaria, as well as indirect effects such as heightened food insecurity and child undernutrition [3,28–32]. In both Burkina Faso and Kenya, climate change exacerbates child undernutrition by compromising food security [30,33,34]. The increasing frequency of severe weather events, such as droughts and floods, reduces crop yields and elevates food prices, leading to inadequate dietary intake and heightened health risks associated with undernutrition [30,33,34]. Chronic undernutrition affects 26% of children under five in Burkina Faso and over 25% in Kenya, contributing to stunting, while acute undernutrition leads to wasting in about 7% of children in Burkina Faso and 4% in Kenya. These conditions have long-term consequences for cognitive and physical development [30]. Moreover, exposure to drought during late childhood and early adolescence has been shown to have persistent adverse effects on growth, primarily mediated by reduced nutritional intake during critical developmental years [35]. In Burkina Faso, studies have demonstrated that rainfall variability directly impacts crop yields and correlates with increased child undernutrition in affected households [36,37].

Despite growing recognition of the impacts of climate change, empirical research on the pathways linking human heat exposure to agricultural outcomes and individual physiological responses remains limited. Comprehensive studies investigating the effects of heat stress on harvest yields, soil quality, plant physiology, livestock health, and farmers’ work capacity are lacking, particularly in SSA [22,23,38,39]. The cascading impacts of heat-induced physiological strain on labor capacity, agricultural productivity, and downstream consequences such as child nutrition are poorly characterized. Moreover, the degree to which these effects are already manifesting in vulnerable populations, and the extent of intra-population variability, remain insufficiently studied. This knowledge gap is largely attributable to limited data availability, underscoring the need for context-specific, empirically grounded research to inform effective adaptation strategies in SSA [40].

To address these gaps on the effects of heat exposure on agricultural productivity and health, the Heat to Harvest (H2H) study investigates the following research questions and corresponding hypotheses.
**What is the impact of heat exposure on the physiological responses of farmers?**
**Hypothesis 1**: Increased heat exposure will significantly elevate physiological strain, as measured by heart rate and body temperature.**How does heat exposure influence farmers’ work capacity and farming behaviors?**
**Hypothesis 2**: Higher temperatures will reduce work capacity and alter farming behaviors, including daily activity patterns, sleep quality, duration, and energy expenditure.**What is the relationship between heat exposure, work capacity, health, and farming practices on harvest yields?**
**Hypothesis 3**: Heat exposure will lead to reduced harvest yields by impairing farmers’ work capacity and health.**How do these factors indirectly affect the nutritional status of children under five in farming households?**
**Hypothesis 4**: Reduced work capacity and lower harvest yields due to heat exposure will negatively impact child nutrition.

This study systematically investigates these pathways using wearable sensors, GPS tracking, offering valuable insights into climate-related challenges faced by subsistence farmers and their families.

## Methods

### Health impact pathways of heat on physiological response, agricultural capacity, harvest yield, and nutritional status of children

The first health impact pathway examines physiological strain due to heat exposure, incorporating temperature, humidity, and the Wet Bulb Globe Temperature (WBGT) index. The WBGT is a standardized composite index that quantifies environmental heat stress by integrating multiple meteorological parameters, including air temperature, relative humidity, and solar radiation. It serves as a physiologically relevant proxy for the subjective perception of heat, capturing the cumulative thermal load experienced by the human body under varying environmental conditions, and is widely employed to assess the potential impact of heat on physical performance and safety. As WBGT levels increase, physical work capacity declines, with significant reductions observed at 27–28°C WBGT [38,41,42].

The second health impact pathway examines the relationship between heat exposure, physiological responses, and work capacity. Prolonged exposure to heat increases cardiovascular strain (above ~26–27°C cardiovascular strain can begin to increase), exacerbates pre-existing health conditions, and heightens the risk of heat-related illnesses, including heat stress, heat stroke, and renal failure. These health effects contribute to reduced work performance, affecting the duration and intensity of agricultural labor. Given that heart rate fluctuations result from both physical exertion and heat stress, careful methodological adjustments will be made to differentiate between these factors (e.g., accounting for cardiac drift in wearable device data).

The third health impact pathway examines how heat affects agricultural work capacity, particularly during peak farming periods such as harvesting. Heat exposure may lead to shortened work shifts, more frequent rest breaks, and reduced overall labor productivity, ultimately impacting both crop yields and harvest quality. This pathway investigates the interplay between heat stress, labor dynamics, and agricultural output, while accounting for variations in socioeconomic conditions, farming techniques, and land use.

The fourth health impact pathway addresses the indirect consequences of heat-induced agricultural disruptions on child nutrition. Declining crop yields and increasing food insecurity may lead to dietary deficiencies, heightened undernutrition, and associated health risks in children under five. By linking environmental stressors to household food availability, this pathway seeks to quantify the nutritional and health impacts of heat exposure on vulnerable populations.

A conceptual framework (refer to Figures 1 and 2 for the conceptual framework of the H2H study and its pathways) illustrates the relationships between heat exposure, physiological strain, agricultural productivity, and child nutrition. The study will incorporate controls for potential confounders to ensure that observed effects can be robustly attributed to heat exposure rather than external factors such as soil fertility, rainfall variability, or market fluctuations.

**Figure 1. f0001:**
[figure not shown]
Conceptual framework of the H2H study.

**Figure 2. f0002:**
[figure not shown]
Pathway of the H2H study, following four health impact pathways: in this study we focus mainly on heat exposure, but also consider the variable of rainfall, its impact on work capacity, physiological responses in farmers, outcomes on harvest yield, and nutritional status in children under age 5.

### Study design

The H2H study will use a prospective cohort design implemented within two established Health and Demographic Surveillance Systems (HDSS): the Nouna HDSS in Burkina Faso (see Figure 3) and the Siaya HDSS in Kenya (see [43] for further details). The Siaya HDSS, operational since 1990, covers a population of about 220,000 across 385 villages in Siaya County, Kenya, an area with a tropical climate, seasonal rainfall (including heavy ‘long’ rains from March to May and ‘short’ rains between October and December), and significant health challenges including endemic malaria, and high rates of HIV and tuberculosis [43,44]. The Nouna HDSS, in operation since 1992, longitudinally observes health and demographic changes among 124,957 individuals in 59 villages and the city of Nouna, Burkina Faso [44]. This area, 300 km northwest of Ouagadougou, experiences a Sudano-Sahelian climate with a long dry season and a short rainy season, receiving an average annual rainfall of 700 mm, with over 30% in August alone [44,45].

**Figure 3. f0003:**
[figure not shown]
Study area (health demographic Surveillance System (HDSS)) with the H2H village in the Kossi province. For the study area of the Siaya HDSS, refer to [43]. Map was generated using QGIS (version 3.16.14; QGIS development team, 2021). QGIS is an open-source geographic information System that supports viewing, editing, and analysis of geospatial data. The software can be accessed and downloaded at https://qgis.org.

### Study participants and sample size

Participants will be randomly selected from both HDSS sites and will include subsistence farmers as well as children residing in their households. A farmer is defined as an individual whose primary occupation is agriculture, evidenced by the active cultivation of at least one food crop, with household livelihood primarily dependent on agricultural production.

The primary outcome variable is heart rate (beats per minute, bpm), used as a physiological proxy for heat-related strain in farmers. Heart rate reflects both physical exertion during agricultural labor and cardiovascular responses to heat stress, making it a key metric for assessing workload intensity and thermal burden. However, as heart rate increases can result from both physical exertion and heat exposure, the study will account for cardiac drift, which refers to the gradual increase in heart rate over time due to prolonged exertion in hot conditions. To differentiate between workload-related heart rate elevations and heat-induced cardiovascular strain, the following strategies will be applied:
Step data and GPS tracking will provide context for exertion levels during work activities.Time-of-day analysis will help distinguish between work-related and heat-related heart rate increases.Cross-referencing heart rate with environmental data (WBGT, temperature, humidity) will enable more precise differentiation between exertion-driven and heat-induced cardiac responses.

To estimate an appropriate sample size for the H2H pilot study, a power analysis is conducted for comparing means between two independent groups:$$n=\frac{2{\left(Z_{\alpha /2}+Z_{\beta }\right)}^{2}\times \sigma^{2}}{\delta^{2}}$$$$n=\frac{2{\left(Z_{\alpha /2}+Z_{\beta }\right)}^{2}\times \sigma^{2}}{\delta^{2}}$$

Where:
n is the sample size required per group.Z_α/2_ is the critical value associated with a desired alpha level (commonly set at 0.05 for a 95- Z_β_ is the critical value associated with the desired power of the test (commonly set at 0.80, yielding a Z_β_ value of 0.84).σ is the standard deviation of the outcome variable, which in this case is the bpm difference.δ is the expected difference in means between the two groups.

A sample size of 63 participants per group is estimated to detect a mean difference of 5 bpm in heart rate with 95% confidence and 80% statistical power. To accommodate potential attrition and inter-individual variability, the H2H study will enroll a total of 210 participants across 25 villages within the HDSS sites during the feasibility phase.

In the Nouna HDSS, the H2H study is nested within a cluster randomized controlled trial (cRCT) evaluating the effectiveness of cool roof coatings as a passive home cooling intervention (DRKS trials registry number DRKS00023207) [46]. Cool roof coatings are designed to reflect solar radiation and exhibit high thermal emittance, thereby reducing indoor temperatures [47].

The cRCT includes 600 households, with 300 households randomly assigned to receive the cool roof intervention and 300 serving as controls. For the H2H study, farmers will be equally sampled from both intervention and control households to ensure balanced exposure conditions. The H2H study does not treat the cool roof intervention as a direct proxy for heat exposure but considers it a potential modifier of recovery following occupational heat stress.

This nested design facilitates the investigation of both direct and indirect heat-related pathways [1]: direct exposure during agricultural work – analyzing physiological responses, work capacity, and productivity; and [2] post-exposure recovery at home, examining whether improved indoor thermal environments enhance recuperation and influence subsequent health and labour outcomes.

While the cool roof cRCT focuses on the effectiveness of home cooling, the H2H study is primarily concerned with occupational heat exposure. Nevertheless, the interaction between workplace heat stress and home-based recovery conditions is a central component in understanding the cumulative effects of heat on health and productivity over time.

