#### Work capacity and physiological response (health impact pathway 2)

To further quantify the relationship between heat exposure and farmers’ work capacity, we will apply a combination of regression models and machine learning techniques. These approaches complement the broader analytical framework by enabling the detection of both linear and non-linear associations between environmental conditions and physiological responses.

Key heat exposure variables – indoor and outdoor temperature, humidity, and Wet Bulb Globe Temperature (WBGT) – will be modeled against continuous physiological indicators such as heart rate, activity levels, and sleep patterns. Linear mixed-effects models will be used to account for within-subject variability and repeated measures, with random effects specified at the individual level to capture heterogeneity in exposure and response. These models will incorporate covariates such as socioeconomic status and farming intensity to control for confounding.

Model validation will involve standard diagnostic tools including residual and Q – Q plots to assess normality, and Variance Inflation Factor (VIF) analysis to detect multicollinearity. In parallel, cross-validation and residual error analysis will be employed to test model robustness and predictive accuracy. Sensitivity analyses will explore how natural variations in environmental conditions – particularly fluctuations in temperature and humidity – affect the stability and reliability of the modeled outcomes.

To enhance the physiological assessment of energy expenditure and physical effort, we will deploy the Renkforce GP-102 GPS Logger, which includes an integrated pedometer function. These devices will collect location and movement data every 15 minutes, allowing for the estimation of energy expenditure based on distance traveled, travel speed, terrain changes, and rest intervals.

Time spent in agricultural fields will be georeferenced, with GPS data linked to each participant’s unique ID and merged with socio-demographic characteristics, field boundaries, and movement patterns. This enables a comprehensive analysis of how mobility and environmental exposure interact to shape work capacity.

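### The 63-per-group, 80% power figure is for a comparison of two unnamed groups, not for the mixed model described for heart rate, the primary outcome

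*Protocol article*

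**What the plan says.** All references are to the protocol article.

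- *Study participants and sample size* names heart rate as the primary outcome. It then says that "a power analysis is conducted for comparing means between two independent groups" and gives the usual two-sample formula. Alpha is described as "commonly set at 0.05". The result is "A sample size of 63 participants per group is estimated to detect a mean difference of 5 bpm in heart rate"; the confidence level is given as 95% and the power as 80%. The groups are not identified and sigma has no value.
- The same section enrols 210 participants in 25 villages over the two surveillance sites. It attributes the margin to attrition and variation between individuals. It gives no site split, attrition rate, intraclass correlation or design effect.
- On the cool-roof trial: "In the Nouna HDSS, the H2H study is nested within a cluster randomized controlled trial". Farmers are to be drawn equally from intervention and control households. The intervention is treated as a possible modifier of recovery, not as a stand-in for heat exposure, and the Abstract says it is not the main focus.
- In the data analysis part, *Work capacity and physiological response (health impact pathway 2)* models temperature, humidity and WBGT against heart rate: "Linear mixed-effects models will be used to account for within-subject variability and repeated measures". Random effects are at the individual level. Table 1 lists the temperature and climate exposures as continuous.

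**The concern.** Hypothesis 1 asks how heart rate responds to heat. The information for that comes from many readings per farmer under varying temperature. The precision of the slope depends on variation within farmers, on the spread of heat exposure, and on how far farmers share the same weather; each site has only five weather stations. A comparison of two independent group means uses none of these quantities.

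The stated power is therefore attached to an analysis that the data analysis section does not describe. Two things follow. The reader does not learn what the study can detect for its primary outcome. And because cool roof against control is the most obvious pair of groups, a null cool-roof or recovery result could be read as coming from a comparison with 80% power, which the plan does not assure. The Conclusion says this phase will inform the main study, so the figure could be carried forward.

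**Working it through.** **1. Reproducing the plan's figure.** Inputs from *Study participants and sample size*: difference 5 bpm, two-sided alpha 0.05 (z = 1.96), power 80% (z = 0.84). Sigma must be assumed.

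n per group = 2 × (1.96 + 0.84)² × σ² / 5²

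With σ = 10: 2 × 7.84 × 100 / 25 = 62.7, rounded up to 63. Other values of σ give 51 (σ = 9), 76 (11), 91 (12) and 142 (15). So the stated 63 implies an SD of about 10 bpm.

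**2. Which two groups?**

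- Hotter against cooler periods: the same farmers contribute to both, so the groups are not independent.
- Nouna against Siaya: no hypothesis compares heart rate between sites.
- Age or gender: used to stratify heat effects, not set out as a comparison of mean heart rate.
- Cool roof against control: the only two-arm contrast described, but stated for Nouna only and given a modifying role.

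No two-group comparison of mean heart rate appears under *Data analysis*.

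**3. If cool roof against control is meant.** Two arms of 63 need 126 farmers in Nouna, and 126 / 210 = 60%, before attrition or clustering. The margin of 210 over 126 would absorb 40% loss (1 − 126/210), but only if all 210 belong to the two arms.

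Power = Φ( 5 / (10 × √(2 × DE / n)) − 1.96 ), with design effect DE = 1 + (m − 1) × ICC.

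Assumptions not in the document: SD 10; the Nouna share; the ICC; m = 210 / 25 = 8.4 farmers per village, pooled over both sites; and villages as the randomised unit. DE is then 1.07, 1.37 and 1.74 at ICC 0.01, 0.05 and 0.10.

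| Nouna share of 210 | n per arm | No clustering | ICC 0.01 | ICC 0.05 | ICC 0.10 |
|---|---|---|---|---|---|
| 40% | 42 | 63% | 60% | 50% | 41% |
| 50% | 52.5 | 73% | 70% | 59% | 49% |
| 60% | 63 | 80% | 77% | 67% | 57% |
| 70% | 73.5 | 86% | 83% | 74% | 63% |
| 100% | 105 | 95% | 94% | 87% | 78% |

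Worked cell, even split without clustering: √(2 / 52.5) = 0.195; 5 / 1.95 = 2.56; 2.56 − 1.96 = 0.60; Φ(0.60) = 0.73. With DE = 1.37: √(2.74 / 52.5) = 0.228; 5 / 2.28 = 2.19; Φ(0.23) = 0.59.

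With 20% attrition and no clustering, power is 63% at an even split (42 per arm), 71% at a 60% share (50.4 per arm) and 90% with all 210 in Nouna (84 per arm).

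The detectable difference at 80% power is 2.80 × 10 × √(2 × DE / n). At an even split this is 5.5 bpm without clustering and 6.4 bpm at ICC 0.05, against the stated 5 bpm.

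**4. The heat slope.** No detectable slope can be computed. The document gives neither the SD of heart rate within farmers nor the spread of heat exposure or the correlation between readings.

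**The case against.** The strongest reply is that the calculation is never tied to the cool-roof arms, so every power figure in the table rests on a guess about the groups. That is right, and it limits the table to illustration. Nothing here shows the study to be underpowered for Hypothesis 1. Up to 12 weeks of monitoring in each of three years may give the slope ample precision.

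Further points stand in part:

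- The parent trial is called cluster randomised, yet the text also says that households were randomly assigned. If households were randomised within villages, the village design effect would not be the right inflation for the arm comparison.
- This is a feasibility phase, and 210 is 67% above 126. That lowers the stakes. It does not make the power claim fit the analysis, since the authors chose to state one.
- The article describes sigma first as the SD of the outcome and then as relating to a difference in bpm. The formula needs the between-person SD. This is a matter of wording in a list damaged in extraction, and it carries little weight.

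Two stronger readings are tempting. A reader might infer that the 80% corresponds to nothing the study intends. But the Abstract does promise a comparison of labor performance and recovery by cool-roof status, and the article names a primary outcome without labelling a primary analysis. A reader might also infer that a central interaction has been left out of the models, because "the interaction between workplace heat stress and home-based recovery conditions is a central component". That sentence concerns recovery conditions at home, not the randomised arm. Indoor temperature, which the roof is meant to change, is already an exposure in the heart-rate model, and exact model terms are commonly left to an analysis plan that is not shown.

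**Conclusion.** The concern holds as a mismatch: the stated sample size and power describe a comparison of two unnamed independent groups, while the analysis described for the primary outcome is a repeated-measures model on continuous heat exposure. The arithmetic behind 63 is sound at an SD of 10 bpm, which should have been stated.

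If the cool-roof contrast was meant, 80% power is not assured. It is reached at a Nouna share of 60% only with no attrition and no clustering. Across an even split and full enrolment in Nouna, power runs from 73% to 95% without clustering, and from 59% to 87% at an ICC of 0.05. These figures rest on an assumed SD, site split, ICC and cluster size. It would be wrong to conclude that the contrast is underpowered; the documents leave that open. Given the feasibility setting, this is a correction worth making but not a critical flaw.

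**What to change.** Rewrite the sample-size paragraph, with enrolment unchanged:

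1. Name the contrast behind the 63 per group, and state the SD and its source.
2. Replace the 80% figure with the heart-rate change per degree that the planned mixed model can detect with 210 farmers, allowing for farmers sharing the same weather on the same day.
3. Report separately, as a secondary figure, the cool-roof difference detectable with the actual Nouna number per arm, the between-person SD, expected attrition, and a design effect for the unit that the parent trial actually randomised. State that unit and the site split.

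Because the Abstract promises a comparison by cool-roof status, terms for randomised arm and arm-by-heat in the Nouna heart-rate and sleep models would be a reasonable, inexpensive addition. They are not the core of this point.

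The cost is one rewritten paragraph and, if adopted, two model terms. The downside is that the cool-roof power figure may look less favourable than the present 80%.
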